### 2.9. Sample size

As this study is a pilot feasibility RCT, one aim is to assess feasibility, refine study procedures, and obtain preliminary estimates of variability to inform sample size for a future definitive RCT. Accordingly, the sample size is based on methodological guidance for pilot studies rather than on a formal power calculation. Following the stepped rule-of-thumb proposed by Whitehead et al.[54], approximately 12 participants per arm (i.e., 24 participants in total) are recommended for early-stage pilot trials with continuous outcomes and small to medium expected effect sizes. In line with this guidance, 24 participants per country (a total of 96) will be recruited for the study. If needed, data can be analyzed separately by country. This sample size is expected to provide sufficient information on feasibility metrics, acceptability of study procedures, and change in the primary outcome.

### 2.10. Assessors and blinding

Outcome assessments at all study sites will be conducted by physiotherapists with at least 2 years of clinical experience with pwMS and prior familiarity with the functional tests included in the protocol. To ensure consistency and standardization across countries, a test manual has been developed detailing all assessment procedures. All assessors will receive instruction and training to perform each test strictly in accordance with this manual. Outcome assessments at both T0 and T1 will be conducted by assessors blinded to group allocation whenever possible. Participants will be instructed not to disclose their treatment allocation during assessments. Standardized assessment procedures will be used across sites.

Any instances of unblinding will be documented.

### 2.11. Data collection, management, and analysis

All study data will be entered directly into a consortium Microsoft SharePoint site, which will serve as the secure, central data repository for the project. SharePoint will be hosted by the University of Limerick, with controlled access provided to all sites. A comprehensive Data Management Plan and Joint Controller Agreement have been developed and signed by all partners prior to study commencement, outlining procedures for data entry, storage, access rights, confidentiality, data protection, and quality assurance. Regular data checks will be performed to ensure completeness and accuracy. Data quality monitoring will be coordinated centrally by [name], who leads the project’s data management work package. Regular consortium meetings and Trial Management Committee/Advisory Board meetings will be held to review data quality and protocol adherence across all participating centers. All procedures will be conducted in accordance with the project Data Management Plan and Joint Controller Agreement. Data for each country will be held locally using relevant procedures and pseudonymized data will be entered into the consortium SharePoint platform held by UL, which serves as the secure central repository for the study. Monthly reviews will be conducted to identify missing data, inconsistencies, out-of-range values, and protocol deviations. Any queries will be communicated to the relevant site for clarification or correction against source. The study will comply with the FAIR data guiding principles [55].

#### Statistical Analysis Plan.

Feasibility outcomes, including recruitment rate, retention rate, adherence, compliance, acceptability, and adverse events, will be summarized using descriptive statistics. Continuous variables will be reported as means and standard deviations or medians and interquartile ranges, as appropriate, while categorical variables will be reported as frequencies and percentages. These outcomes will be used to assess the feasibility of conducting a future definitive trial.

Baseline demographic and clinical characteristics will be summarized using appropriate descriptive statistics. Variables with a normal distribution will be reported as mean and standard deviation, while non-normally distributed variables will be summarized as median and interquartile range. To examine changes in outcomes from baseline to the end of the intervention period, a multivariate repeated-measures mixed-effects regression model will be applied. Participant ID will be included as a random effect, and group (intervention vs. comparator) and time (T0 vs. T1) will be included as fixed effects. The model’s assumptions, including normality of residuals and homogeneity of variance, will be assessed using graphical and statistical methods. If these assumptions are not met, appropriate data transformations, non-parametric methods, or other alternative statistical approaches will be considered.

The primary analysis will adhere to the intention-to-treat principle, ensuring that all randomized participants are analyzed in the groups to which they were originally assigned, irrespective of adherence or protocol deviations. A secondary per-protocol analysis will be conducted, including participants who complete the post-intervention assessment and meet the predefined adherence (≥80%) and compliance (≥75%) criteria. Sensitivity analyses will be performed to assess the impact of missing outcome data and to compare findings obtained from the intention-to-treat and per-protocol populations. Robustness will be evaluated by examining whether the overall direction and interpretation of the results remain consistent across these analyses.

### 2.12. Stakeholder and Patient Involvement

An external advisory board will provide independent scientific oversight and trial management. Furthermore, each site has established a patient panel of 3–4 pwMS, who have guided the development of this protocol and will provide feedback on recruitment material. Following study completion, the patient panels will be actively involved in discussions about the overall feasibility and effectiveness, and whether to proceed to a full trial. Additionally, they will advise on and be part of the dissemination to ensure that results are communicated clearly and meaningfully.

### 2.13. Ethical consideration, declarations, and dissemination

This study protocol adheres to the Standard Protocol Items: Recommendations for Interventional Trials (SPIRIT) guidelines. All participating sites have obtained approval from their respective ethics committee (Israel: Sheba Medical Center IRB Journal no. SMC-2730-25, Ireland: Education and Health Sciences Research Ethics Committee Journal no. 2025_01_17_EHS, Italy: Comitato Etico Sardegna Prot Journal no. Prot. 21448, Denmark: Journal no. 1-10-72-196-25. The study is registered at ClinicalTrials.gov (NCT07310914) and adheres to the principles outlined in the Declaration of Helsinki and its later amendments. All participants will provide written informed consent using forms approved by the local ethics committees. Results from the study will be disseminated in international peer-reviewed journals, regardless of whether the findings are positive, negative, or neutral.

### 2.14. Current trial status

Recruitment has not yet begun. It is expected that recruitment will be completed by the end of 2026 and that data collection will be completed early in 2027. Results are expected to be published in 2027.

## 3. Discussion

This protocol describes a pilot feasibility RCT designed to evaluate an advanced TR intervention incorporating MoveAI for pwMS.

### Strengths and Limitations

A major strength of the study is the novelty of the intervention (details on the MoveAI features have been outlined above). If found feasible, the approach may help overcome access barriers for pwMS who have difficulty attending in-person rehabilitation and extend the effects of intensive rehabilitation/exercise interventions administered through national health systems, but that are limited in time due to budget constraints. Another strength is the integration of both patient-reported outcomes and objective system-generated mobility data, providing a multidimensional understanding of how the TR system and training program may function in real-world settings. The study also includes a relatively large sample (n = 96) for a pilot RCT across multiple international sites, enhancing the robustness of the feasibility and effectiveness metrics and later implementation into practice.

Importantly, several limitations should also be acknowledged. As a TR intervention, technical challenges, including device compatibility, network connection stability, and varying levels of digital literacy, can affect the delivery of the intervention and participant engagement. These challenges will be monitored throughout the trial and reported as part of the feasibility outcomes. Physical activity outside the intervention will be assessed using self-reported diaries, which may introduce recall bias; objective activity trackers would provide complementary real-world data, but their use is beyond the scope of this study. Finally, as a feasibility trial, the study is not powered to detect efficacy, and any observed clinical trends will be interpreted cautiously.

### Operational Considerations, Amendments, and Dissemination

Because this study involves sites from different countries and operational systems, differences in site logistics, staffing, and local clinical practices may influence recruitment rates and adherence, and hence each country has sufficient numbers for its own pilot study analysis. Standardized training and regular cross-site communication will be used to minimize variability. Any protocol amendments will require approval from the consortium, the advisory board of three MS rehabilitation experts, and all relevant institutional ethics committees. The study may be paused or terminated if major unforeseen safety or operational concerns arise.

Findings from this feasibility trial will inform the design of a future fully powered RCT. Regardless of outcome (positive, negative, or neutral), results will be disseminated through peer-reviewed publications, conference presentations, and patient-focused communication materials co-created with patient panels at each site.

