### 2.5. Randomization

Participants who meet all eligibility criteria and complete the baseline evaluation will be randomly assigned at each site in a 1:1 ratio to either the TR intervention group or the paper-based exercise group. A computer-generated randomization sequence stratified by study site will be used. Randomization procedures at all sites will be coordinated according to a common study protocol developed by the project team. Allocation concealment will be ensured using sequentially numbered, opaque, sealed envelopes prepared and maintained locally at each participating site. Envelopes will be opened only after eligibility has been confirmed and baseline assessments have been completed.

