An ***economic evaluation*** will be performed from both health-system and societal perspectives. The economic evaluation methodology, data collection procedures, and resource-use measures were developed with input and guidance from a health economics expert within the PLATINUMS consortium to ensure the appropriateness of the proposed approach. Participant-level resource use, including healthcare and social care contacts, informal caregiving, productivity loss, medication use, assistive devices, and out-of-pocket expenses, will be assessed using an adapted Client Service Receipt Inventory (CSRI) [48]. Provider and system-level costs (e.g., platform setup, operational resources, staff training, therapist time, clinical space, administrative support, printed materials) will be captured using standardized implementation cost forms. Quality-adjusted life years (QALYs) will be derived from EQ-5D utilities using the area-under-the-curve method, and costs and QALYs will be compared between study arms to compute the Incremental Cost-Effectiveness Ratio (ICER) [49].

Feasibility of the trial. To assess the feasibility, we will evaluate 1) recruitment and retention rates, 2) evaluation of data collection procedures, 3) evaluation of acceptability of the interventions and study procedures, 4) evaluation of the ability of the consortium to manage the study, 5) safety of the interventions, and 6) preliminary measures of effectiveness of participant responses to the intervention.

When evaluating recruitment rates, we will determine whether 8 months is an acceptable time frame for recruiting 96 participants across 4 sites. To evaluate the data collection and intervention procedures, our semi-structured interviews with participants in each country will help us determine them. For the intervention’s acceptability, we consider an 85% retention rate acceptable and will explore this further in the semi-structured interviews. Furthermore, we will use the Telehealth Usability Questionnaire (TUQ) [50] to assess the usability of the TR system. Trial management will be overseen by an external advisory board. Adverse events (AEs) will be closely monitored throughout the study period, and rates will be compared with those in other exercise intervention studies [51].

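### Each country's target equals the pilot benchmark of about 12 per arm with no allowance for loss, so country-level sufficiency is not supported for outcomes that need the 10-week assessment

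*Protocol article*

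**What the plan says.** Section 2.9 (Sample size) explains that "the sample size is based on methodological guidance for pilot studies rather than on a formal power calculation". The guidance it relies on is that "approximately 12 participants per arm (i.e., 24 participants in total) are recommended for early-stage pilot trials with continuous outcomes", and from this it concludes that "24 participants per country (a total of 96) will be recruited for the study". One listed aim of the sample is to "obtain preliminary estimates of variability to inform sample size for a future definitive RCT", and the section expects the sample to be informative about change in the primary outcome. It adds: "If needed, data can be analyzed separately by country".

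Section 2.5 (Randomization) has participants "randomly assigned at each site in a 1:1 ratio to either the TR intervention group or the paper-based exercise group", stratified by site, which gives about 12 per arm in each country.

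Section 2.7 (Outcomes) measures the primary outcome at baseline (T0) and at 10 weeks (T1). On retention it says "we consider an 85% retention rate acceptable".

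The Discussion, under Operational Considerations, Amendments, and Dissemination, notes that logistics, staffing and local practice may affect recruitment and adherence, and infers that "each country has sufficient numbers for its own pilot study analysis".

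**The concern.** The benchmark and the recruitment target are the same number, so there is no room for loss. Any participant without a T1 assessment takes that arm of that country below 12 for the analysis of change. The plan itself would regard a trial that loses 15% as acceptable. Nothing links that tolerance to the claim of sufficiency, and the claim covers a whole pilot analysis rather than only the feasibility measures.

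What is at stake is how country results may be read. A reader who takes the sentence at face value could treat a national estimate of change in the 30-second sit-to-stand test, or its SD, as adequately supported by the plan. The pooled analysis is not affected.

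**Working it through.** **Inputs.** About 12 per arm and 24 per country in four countries (section 2.9); 1:1 allocation within site (section 2.5); 85% retention as the acceptable level (section 2.7); T1 needed for change (section 2.7). No significance level, power, effect size or SD is used in the plan, so no power formula applies.

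**1. The plan's own figure.** 12 × 2 arms × 4 countries = 96. This reproduces exactly, with zero inflation for loss.

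**2. Numbers with T1 data at 85% retention.**
- Per arm per country: 12 × 0.85 = 10.2, about 10.
- Per country: 24 × 0.85 = 20.4, about 20.
- Overall: 96 × 0.85 = 81.6, about 82; per arm 48 × 0.85 = 40.8, about 41.

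**3. Other retention levels.** Per arm per country: 12 × 0.95 = 11.4 and 12 × 0.90 = 10.8. If each participant independently has an 85% chance of being retained, one arm keeps all 12 with probability 0.85^12 = 0.14, and both arms of a country do so with probability 0.14² = 0.02.

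**4. What 12 evaluable per arm would require at 85%.** 12 / 0.85 = 14.1, so 15 per arm, 30 per country and 120 in total.

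**5. Effect on precision.** The 95% limits for an SD, as multiples of the estimate, are √(df/χ²₀.₉₇₅) and √(df/χ²₀.₀₂₅). The 95% half-width for an unadjusted difference between arms, in SD units, is t₀.₉₇₅ × √(2/n).

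| Sample | n per arm | df | SD limits | Half-width |
|---|---|---|---|---|
| One country, no loss | 12 | 22 | 0.77 to 1.42 | 2.074 × √(2/12) = 0.85 SD |
| One country, 85% retained | 10 | 18 | 0.76 to 1.48 | 2.101 × √(2/10) = 0.94 SD |
| Pooled, 85% retained | 41 | 77 | 0.86 to 1.19 | 1.99 × √(2/41) = 0.44 SD |

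The pooled df is 82 − 2 arms − 3 further site terms = 77, which assumes four sites. If the two Danish hospitals count as separate sites, the df falls by one and the result hardly changes.

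The required size of a later trial scales with the variance. An SD limit of 0.76 to 1.48 therefore corresponds to a 0.57- to 2.2-fold range in sample size (0.756² = 0.57; 1.479² = 2.19). The pooled limits give about 0.75- to 1.41-fold (0.864² = 0.75; 1.187² = 1.41).

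**6. A feasibility measure on the full denominator.** Retention is counted on all recruited, so loss does not shrink this sample. The exact (Clopper-Pearson) 95% interval for 20/24 is 63% to 95%; for 82/96 it is 77% to 92%. A country-level percentage can be described, but it needs its interval beside it.

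**The case against.** The strongest reply is that section 2.9 applies the benchmark to recruited participants and nowhere says evaluable. On that usage 24 per country meets it, and nothing is wrong arithmetically. Whether the cited guidance means recruited or evaluable cannot be checked from the document. This stands, and it rules out saying that the plan breaks its own rule.

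Three further replies also stand. The 85% is a threshold of acceptability, not a forecast of loss. The reason given in the Discussion is variation in recruitment and adherence, which are described on all 24. And the step from 12 to 10 per arm barely moves precision: most of the imprecision in a single country is there at 12.

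The analysis of all randomised participants with a mixed model helps less. Someone seen only at T0 contributes a baseline value but no observed change, so the information on change and its SD still comes mainly from those with T1 data.

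A reader might infer more than the text supports:
- That a country could miss the retention criterion by chance and so count against the trial. The plan states one retention level and never applies it country by country.
- That a country-level SD will size the definitive trial. No section says so.
- That the wording about separate analysis if needed permits a split chosen after seeing the data. What triggers such an analysis is detail that a protocol article may leave to the analysis plan.

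**Conclusion.** The point holds in a limited form. The per-country target carries no allowance for loss, and at the retention level the plan accepts, about 10 per arm per country would have T1 data. The unqualified statement of sufficiency is therefore not supported for change in the 30-second sit-to-stand test and its SD. It is supported for feasibility measures described on all recruited participants, and it is met outright if the benchmark counts recruitment.

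The shortfall is about 2 per arm per country, and its own effect on precision is small. The larger contrast is between any single country (half-width 0.85 to 0.94 SD) and the pooled sample (0.44 SD), which is why planning should rest on the latter. These figures assume equal loss in both arms, a common SD, and retention exactly at 85%.

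**What to change.** - In section 2.9 and under Operational Considerations, limit the country-level statements to descriptive reporting of feasibility measures, with confidence intervals.
- In section 2.9, say whether about 12 per arm means recruited or evaluable participants. State that, if retention were at the 85% acceptability level, about 82 participants (41 per arm), or about 20 per country, would be evaluable at T1.
- State that the pooled analysis of all 96 is the basis for effect estimates, and that its pooled within-site SD is the basis for sizing the definitive trial. Add site to the model in the Statistical Analysis Plan part of section 2.11: site is the randomisation stratum, but the fixed effects listed there are only group and time.

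The cost is the option of separate national effect analyses. The first two items are wording only; the third changes the stated model. Section 2.14 says recruitment has not begun, so all three can be settled beforehand without raising the recruitment target. If national analyses of change are wanted after all, the alternative is to recruit 120 (30 per country), which keeps about 12 evaluable per arm at 85% retention but still leaves each country imprecise.

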### Perspectives

Although feasibility outcomes must be interpreted within the scope of an early-stage evaluation, the successful implementation of MoveAI could represent a meaningful advance in MS TR. Beyond supporting exercise participation and motivating adherence and compliance, continuous tracking of movement patterns may eventually help identify subtle functional decline and inform more personalized, timely rehabilitation strategies.
